**Fig. 1 Fig1:**
[figure not shown]
Study design. The control group will be treated with intravenous loop diuretics by experienced HF cardiologists according to guideline recommendations. Patients of the early UF group will receive a single or repeated session of UF started within 24 h from admission until the relief of patient’s symptom. HF, heart failure; UF, ultrafiltration

The trial aims to recruit 40 patients (20 patients for each group) over an estimated 24-month period. After baseline visit, follow-up visit will occur at the end of study treatment, 24 h, 48 h, and 72 h after the end of study treatment, at discharge, and 30 days after discharge. At the baseline visit, informed consent will be taken, and additional baseline variables including gender, age, height, weight, occupation, race, physical activity, complete medical history (including history of smoking and drinking, past and present medical history, concomitant disease), vital signs, NYHA classification, dyspnea severity score, score by Minnesota Living with Heart Failure Questionnaire (MLWHFQ) functional capacity, physical examination including distention of jugular vein, edema of lower extremity and congestion of other organs, laboratory test, electrocardiogram, chest X-ray, echocardiographic data and concomitant drug used up to 3 months before enrollment will be recorded.

Questionnaires (dyspnea severity score and score by MLWHFQ functional capacity) at follow-up visits will also be collected by trained clinicians. This will aid in our assessment of patients’ cardiac function and other safety data.

During follow-up, we will record all the primary and secondary end points and adverse events. All adverse events will be evaluated according to severity, causality, expectedness, and relationship to study treatment. Subjects who develop complications that, in the judgment of principal investigator or sub-investigator, are not suitable to continue the trial will be screened out from the study. Participants will continue with follow-up and may restart study protocol if the clinical situation resolves. Investigators are responsible for the decision to resume the study. If treatment according to the study protocol is clinically insufficient, the study will be suspended and effective treatment should be applied according to the current clinical practice.

Blinding cannot be realized because of different decongestion methods used in the 2 groups. A researcher who is unaware of the treatment group will adjudicate all endpoint events and another researcher who is also blinded to the patient allocation is assigned for the statistics task.

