### Study overview

The EUC-CHF trial is an open-label, registry-based, prospective, single center study. It will recruit patients with severe acute decompensated HF who are hospitalized for HF worsening and significant weight gain due to overt fluid overload 24 h from hospital admission. The determination that acute decompensated HF is the primary cause of hospitalization will be made by the site’s principal investigator or sub-investigator, based on the assessment of the clinical signs and symptoms as well as laboratory examinations that lead to the admission. Patient enrollment should be completed and study treatment initiated within 24 h from hospital admission. Patients will be enrolled 1:1 sequentially to receive standard medical therapy (control group) or early UF (early UF group). Up to 2 doses of IV LDs will be allowed before enrollment.

The diuretic protocol adopted by our study in the control group refers to the protocol of AVOID-HF and CARRESS-HF trial as well as the dose recommended by the guideline according to patients’ vital signs, status of hemoconcentration, and renal function (Table 1) [10, 11]. Patients of the early UF group will be treated with a single or repeated session of UF within 24 h from admission (according to local clinical practice and with availability of nursing surveillance during UF) until the relief of patient’s symptom. The UF protocol adopted by our study also refer to the protocol of AVOID-HF and CARRESS-HF trial (Table 2).

[figure not shown]

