### Study outcomes

The primary end points of EUC-CHF are the changes of weight loss and dyspnea severity score at every scheduled visit which are considered as the part of a single composite endpoint, as well as the occurrence of clinically major bleeding defined by TIMI or GUSTO criteria [12].

Secondary outcomes include: net fluid loss, length of stay in CCU or ICU, change of score by MLWHFQ functional capacity, change of serum and ultrafiltrate concentrations of endotoxin, ET-1, TNF-a, IL-6 and IL-10, changes of cardiac function (the NYHA classification), changes in N-terminal proB-type natriuretic peptide (NT-proBNP) level, changes of LDs dose, HF rehospitalizations for congestive HF in 30 days after discharge, cardiovascular death and all-cause death in 30 days after discharge, change of blood pressure, changes in hepatic and renal function (serum creatinine concentration, estimated glomerular filtration rate [eGFR]), serum electrolytes, hemoglobin and incidence of acute coronary syndrome at scheduled visits.

Weights will be obtained at every scheduled visit using the same balance with the patient shoeless in a hospital gown after emptying the bladder. Weight loss is the difference between weight at baseline and the weight recorded at subsequent visits.

The dyspnea severity score by a proposal to standardize dyspnea measurement in clinical trials of acute heart failure syndromes by International Working Group on acute heart failure of European Society of Cardiology is used for the assessment of dyspnea [13].

Total fluid intake and output (ultrafiltrate and urine) measured at every scheduled visit after enrollment will be used to calculate net fluid losses.

Glomerular filtration rate will be calculated according to the abbreviated Modification of Diet in Renal Disease (MDRD) equation [14].

Acute coronary syndrome includes unstable angina, ST segment elevated myocardial infarction and non-ST segment elevated myocardial infarction. Myocardial infarction is defined according to the fourth universal definition of myocardial infarction [15]. Death will be considered cardiac according to the 2014 ACC/AHA key data elements and definitions for cardiovascular endpoint events in clinical trials [16].

We also will collect all the urine output after patients are enrolled to receive standard medical therapy or early UF until 72 h after the end of study treatment. Then we will measure the average urine electrolytes for every enrolled patient.

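### In-hospital primary assessments are timed from the end of study treatment or at discharge, not from enrolment, so the arms are likely to be compared at different elapsed times

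*Protocol article*

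**What the plan says.** **Visit schedule** (Methods/design, Study overview, text after Fig. 1). After baseline, "follow-up visit will occur at the end of study treatment, 24 h, 48 h, and 72 h after the end of study treatment", then at discharge and 30 days after discharge. The readable text gives no post-baseline visit at a set time from enrolment or from the start of treatment.

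**Primary efficacy endpoint** (Study outcomes). It consists of "the changes of weight loss and dyspnea severity score at every scheduled visit which are considered as the part of a single composite endpoint". Weight is cumulative: "Weight loss is the difference between weight at baseline and the weight recorded at subsequent visits".

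**Fluid measures** (Study outcomes). For the secondary endpoint, "Total fluid intake and output (ultrafiltrate and urine) measured at every scheduled visit after enrollment will be used to calculate net fluid losses". Urine is collected from enrolment "until 72 h after the end of study treatment".

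**End of UF.** Study overview and the Fig. 1 legend run UF "until the relief of patient’s symptom". Table 2, section D, lists four alternative grounds for considering completion: resolved congestion (which includes absence of orthopnea), best achievable dry weight, a persistent creatinine rise, and persistent haemodynamic instability. All depend on how the patient responds.

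**End of control treatment.** The readable text gives no rule. Table 1, which holds the control regimen, is not shown.

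**Expected speed.** The Background describes UF as possibly the more rapid way to remove fluid.

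**Analysis** (Statistical analysis). Kaplan-Meier, log-rank and Cox are named for the primary efficacy endpoint, with 20 patients per group and two-sided tests at 0.05.

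**The concern.** Weight loss from baseline, net fluid loss and dyspnea all change with elapsed time. If the clock for reading them starts when treatment ends, and treatment ends when the patient has responded, two things follow.

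First, a matched visit such as 24 h after treatment falls at a different time since enrolment in each arm whenever the courses differ in length. Part of any observed difference, or of any absence of difference, then reflects treatment duration.

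Second, a UF patient who stops because symptoms have eased arrives at the end-of-treatment dyspnea assessment already improved, because improvement is what triggered the visit.

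Both parts of the primary efficacy endpoint are affected. If dyspnea is not scored at common times, it is unlikely to be recoverable afterwards.

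**Working it through.** The plan states no figure that this point could reproduce: the 40 patients are given without effect size, SD or power. The check is a reading of the schedule, followed by illustrations that rest on assumptions.

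**1. Which clock applies.** The visits are end of treatment, +24, +48 and +72 h, discharge, and discharge + 30 days. With T the treatment duration, elapsed time since treatment start at the four treatment-anchored visits is T, T + 24 h, T + 48 h and T + 72 h. Discharge is also a post-enrolment event. No visit is common to both arms in time since enrolment unless T is the same.

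**2. How much T can vary within the UF arm.** Table 2 gives initial rates of 150, 200 or 250 cc/hr, less 50 cc/hr with listed features, so 100 to 250 cc/hr. Assume 2 to 5 L removed (not in the documents). Duration = volume / rate:
- 2 L: 2000/250 = 8 h to 2000/100 = 20 h
- 5 L: 5000/250 = 20 h to 5000/100 = 50 h

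The +24 h visit then falls 8 + 24 = 32 h to 50 + 24 = 74 h after UF start. These durations ignore holds and the rate reductions that Table 2 expects.

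**3. A spurious difference where none exists.** Assume the same weight-loss curve in both arms, 6 kg × (1 − exp(−t/2)), t in days, with UF lasting 1 day and diuretics 2 or 3 days. The gap at k days after treatment is 6 × [exp(−(1+k)/2) − exp(−(T_control+k)/2)].

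| Visit | 1 vs 3 days | 1 vs 2 days |
|---|---|---|
| End of treatment | 6 × (0.607 − 0.223) = 2.30 kg | 6 × (0.607 − 0.368) = 1.43 kg |
| +24 h | 6 × (0.368 − 0.135) = 1.40 kg | 6 × (0.368 − 0.223) = 0.87 kg |
| +48 h | 6 × (0.223 − 0.082) = 0.85 kg | 6 × (0.223 − 0.135) = 0.53 kg |
| +72 h | 6 × (0.135 − 0.050) = 0.51 kg | 6 × (0.135 − 0.082) = 0.32 kg |

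For scale, a two-sided t-test with 20 per arm (SE = SD × √(2/20); noncentral t, 38 df), using the 1 vs 3 day gaps, would reject as follows. At end of treatment: 94%, 66% or 43% for SD 2, 3 or 4 kg. At +72 h: 12%, 8% or 7%. The plan names a different analysis for the primary endpoint, so these are not error rates for this trial.

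**4. A real difference that is hidden.** Step 3 does not let response decide when treatment stops. Suppose it does: both arms stop at a loss of 2 kg, UF removes 2 kg/day and diuretics 1 kg/day (all assumed). Then T = 2/2 = 1 day and 2/1 = 2 days. At end of treatment the loss is 2 kg in each arm, a difference of 0. At 24 h from treatment start it is 2 kg versus 1 kg, a difference of 1 kg. The end-of-treatment visit erases a true difference in speed.

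**5. The time-to-event analysis.** If time runs from enrolment, no scheduled visit can record improvement before treatment ends, so the earliest event time is T. If time runs from end of treatment, UF patients stopped for relief tend to have their event at time zero. Neither origin removes the dependence on T.

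**The case against.** Comparing completed courses of two strategies is a legitimate question, and several stronger readings do not hold.

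- **That treatment duration is shown to differ by arm.** A reader might infer this as fact. The control stopping rule may be in Table 1, and Fig. 1, which summarises the visit schedule, is not shown either. The difference is an inference from the Background's expectation that UF is faster. It survives a common response-based rule, because time to response would still depend on how fast each treatment works.
- **That the UF arm's end-of-treatment dyspnea score is fixed by the stopping rule.** Table 2, section D, also lets UF end for creatinine, instability, or poor tolerance at best achievable dry weight, and section E provides for patients who stop without adequate decongestion. Its congestion criterion uses jugular pressure, orthopnea and edema, not the dyspnea severity score. The conditioning is partial and applies to those who stop on relief.
- **That the illustrated rejection rates describe this trial.** Curve, durations and SD are assumed, the stop times in step 3 are not response-based, UF patients keep losing weight along the curve although Table 2 aims for even balance once dry weight is reached, and the t-test is not the planned primary analysis.
- **That the bias persists through all visits.** In the illustration most of it has gone by +72 h.
- **That no analysis could repair it.** For weight, analysis on actual elapsed time could reduce the misalignment, and charted weights may exist. For dyspnea, which is collected at the follow-up visits, nothing in the text shows that common-time scores would be available.

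What remains is that the readable schedule has no common-time assessment, that it feeds the primary endpoint, and that its clock depends on response in at least one arm.

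**Conclusion.** The concern holds in this limited form. As the article reads, every in-hospital primary assessment is tied to the end of study treatment or to discharge, and the end of UF depends on response. Elapsed time since enrolment at matched visits is likely, though not shown, to differ between arms. Cumulative weight loss, net fluid loss and dyspnea can be biased in either direction: step 3 creates a difference from nothing and step 4 hides a real one.

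The effect is greatest at the earliest visits and smaller by +72 h. The documents do not allow its size to be derived; the figures above show only that, under the assumptions stated, it ranges from a fraction of a kilogram to more than two.

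**What to change.** Add weight, dyspnea score and cumulative fluid balance at the same times from enrolment or start of study treatment in both arms, for example 24, 48 and 72 h, whether or not treatment is still running. Base the primary efficacy comparison on one of these times. For any time-to-event analysis, take enrolment or treatment start as the time origin. Keep the end-of-treatment visits as secondary or descriptive. Treatment and its stopping rules are untouched.

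The cost is a schedule amendment and a few extra bedside assessments, some of them during a running session. For patients already enrolled (recruitment began in December 2018), weights may be approximated from charts, but dyspnea scores at the new times may not be recoverable.

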### Statistical analysis

We will compare estimates of patients who receive UF therapy with those who receive conventional pharmacologic therapy. Concomitant medication and other baseline characteristics will be utilized in subgroup analysis.

Continuous variables will be summarized using descriptive statistics. Qualitative variables will be summarized by counts and percentages.

We will compare baseline characteristics. T-test or sign rank test will be used after testing for normality. Chi-square or Fisher’s exact test will be performed for categorical variables.

The primary efficacy endpoint (change of weight loss and dyspnea severity score) will be analyzed by Kaplan-Meier method, and comparisons between two groups will be performed using a log-rank test. Hazard ratio with 95% CI will be derived by the Cox proportional hazards model. Subgroup analyses of the efficacy endpoint are performed for the evaluation of impact of major clinical features on the improvement of primary efficacy endpoints by early UF therapy. Specific information is as follows:

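### The follow-up rules say both that patients with complications leave the study and that they stay in follow-up, and the comparison is worded by treatment received, so such patients could be dropped or reclassified

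*Protocol article*

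**What the plan says.** Four statements in the follow-up paragraph of the Study overview (after the Fig. 1 legend) bear on this.

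- Recording: "During follow-up, we will record all the primary and secondary end points and adverse events".
- Removal: subjects with complications who, in the judgement of the principal investigator or a sub-investigator, "are not suitable to continue the trial will be screened out from the study".
- Continuation, in the very next sentence: "Participants will continue with follow-up and may restart study protocol if the clinical situation resolves". On re-entry: "Investigators are responsible for the decision to resume the study".
- Insufficient treatment: "If treatment according to the study protocol is clinically insufficient, the study will be suspended and effective treatment should be applied".

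The blinding paragraph that follows says the treatments cannot be masked, but "A researcher who is unaware of the treatment group will adjudicate all endpoint events", and a second blinded researcher does the statistics.

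Study outcomes makes major bleeding part of the primary endpoint: "as well as the occurrence of clinically major bleeding defined by TIMI or GUSTO criteria". Statistical analysis opens with the comparison: "We will compare estimates of patients who receive UF therapy with those who receive conventional pharmacologic therapy". The planned size is 40 patients, 20 per group, enrolled 1:1 in sequence.

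**The concern.** Leaving the study and staying in follow-up are different rules. They give different data after the complication and different denominators. The article states both and does not say which governs.

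The trigger for removal is a complication, and it is tied to outcome and to arm. Major bleeding is a primary endpoint, and only the ultrafiltration (UF) group has protocol-specified heparin and a large venous catheter. The judgement on removal and on re-entry is made by investigators who know the treatment. A blinded adjudicator and a blinded statistician do not repair this if patients or their later data are taken out before reaching them.

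The wording by treatment received adds a second route. Table 2, parts D and E, lets UF end for instability or a creatinine rise and then, without adequate decongestion, start IV diuretics. The follow-up paragraph also provides for other treatment when protocol treatment is insufficient. Some UF-group patients may therefore receive both therapies, and the comparison sentence does not say where they count.

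At stake is the aim in the Background and abstract: superiority over IV loop diuretics without adverse events. That conclusion needs the patients with complications in both numerator and denominator. So does the stated search for factors linked to non-response to UF.

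**Working it through.** **Step 1: the sentences side by side.**

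| Question | Text that points to leaving | Text that points to staying |
|---|---|---|
| Is the patient still in the study? | "are not suitable to continue the trial will be screened out from the study" | The sentence after it: follow-up goes on and re-entry is possible |
| Are later outcomes collected? | Not if the patient is out of the study | "During follow-up, we will record all the primary and secondary end points and adverse events" |
| In which group is the patient counted? | "We will compare estimates of patients who receive UF therapy with those who receive conventional pharmacologic therapy" (by treatment received, if literal) | Enrolment 1:1 to one of two groups |

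The first two rows conflict within one paragraph. The third is ambiguous. Nowhere does the article say that removed patients are excluded from analysis, or how switched or suspended patients are classified.

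**Step 2: the plan's own figure.** The only relevant figure is 20 per group. It cannot be reproduced, because the article gives no effect size, SD, event rate, power or dropout. For scale, 20 per group gives 80% power for a standardised difference of about 0.89 and 90% for about 1.03 (normal approximation, two-sided 0.05). One patient is 1/20 = 5% of an arm.

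**Step 3: possible size, on the assumption (not in the article) that removed patients leave the analysis.**

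*Bleeding.* If the true rate is p and a share q of the patients with bleeding is dropped, the observed rate is p(1 − q)/(1 − pq). The values of p are assumed.

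| True p | q = 0 | q = 0.5 | q = 1 |
|---|---|---|---|
| 5% | 5% | 2.6% | 0% |
| 10% | 10% | 5.3% | 0% |
| 20% | 20% | 11.1% | 0% |

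Example: 0.10 × 0.5/(1 − 0.05) = 0.0526. In counts, three bleeds in 20 are 15% (exact 95% CI 3.2% to 37.9%). If all three patients were deleted, the table would show 0/17, with upper limit 1 − 0.025^(1/17) = 19.5%.

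*Response.* Assume 60% responders in both groups (12/20) and drop k non-responders from UF only. The UF rate becomes 12/(20 − k): 63%, 67%, 71% and 75% for k = 1 to 4.

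*Continuous outcome.* Simulation with 200,000 runs, normal data, no true effect and a pooled t-test, dropping the k worst of 20 UF patients:

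| k | Shift in UF mean (SD) | Two-sided type I error |
|---|---|---|
| 0 | 0.00 | 0.050 |
| 1 | 0.10 | 0.068 |
| 2 | 0.18 | 0.101 |
| 3 | 0.26 | 0.145 |
| 4 | 0.33 | 0.199 |

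This is a worst case: removals in one arm only, and always the poorest responders. It uses means, whereas the article plans Kaplan-Meier, log-rank and Cox analyses, which were not simulated. In those analyses a removed patient would ordinarily be censored, and censoring because of a complication would be informative.

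**Step 4: after the fix.** With every patient kept and analysed in the group of enrolment (k = 0, q = 0), there is no shift, type I error is 0.050, and the observed bleeding rate equals the true rate.

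**The case against.** The strongest reply is that the paragraph, read as a whole, describes an interruption of study treatment with follow-up kept: a patient who may restart has not left the trial. A major bleed that leads to removal has already happened, falls under the recording of all endpoints and adverse events, and goes to a blinded adjudicator. The comparison sentence may simply name the two arms, since Study overview and Study outcomes use the same verb for what patients are enrolled to receive. Unattainable venous access is an exclusion criterion, so recognised access failure is largely screened before enrolment. IV diuretics after UF are part of the UF group's own protocol, so their use is not in itself a crossover. The removal rule covers both arms, so the direction of any bias is open. Analysis sets may be defined in a full protocol or analysis plan that is not shown.

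Most of this stands. A reader might infer that bad outcomes do leave the analysis and that efficacy and safety are therefore biased. The article does not support that, because no sentence removes anyone from an analysis. The 0/17 example needs every recorded bleed to be deleted together with its patient, and nothing provides for that. The absence of a named analysis set is not the point either.

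What the reply does not remove is the stated conflict. Recording an event does not settle whether the patient stays in the denominator, or whether later weight, dyspnea and 30-day outcomes count. The benign reading has to be chosen by the reader, because the text also states the other one.

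**Conclusion.** The point holds as a contradiction and a badly fixed rule, not as a demonstrated bias. The follow-up paragraph both removes and retains patients with complications, at the judgement of unblinded investigators, and Statistical analysis words the comparison by treatment received. A literal reading permits outcome-related removal or reclassification.

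The firm figure is that each patient is 5% of an arm. The shifts of about 0.18 or 0.26 SD for 2 or 3 dropped patients, and the bleeding figures, rest on three assumptions that the article does not state: removed patients leave the analysis, they leave one arm only, and (for the shifts) they are the poorest responders. If follow-up data are kept and analysed by group of enrolment, none of this bias arises.

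**What to change.** 1. Study overview, follow-up paragraph: reconcile the two sentences. State that being screened out means discontinuing study treatment only, and that the patient keeps all scheduled visits with endpoints and adverse events recorded. Say the same for patients whose protocol treatment is judged insufficient and who are given other treatment.
2. Statistical analysis, opening sentence: reword so that the primary, secondary and safety comparisons include every enrolled patient in the group to which the patient was enrolled, whatever treatment was received or changed. Show results by treatment received only as a sensitivity analysis.

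When treatment is stopped or restarted is a clinical matter and is not changed by this. The cost is wording in two places. Continued follow-up is already planned, so no new visits or measurements are needed, and no revised sample size follows.
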